## Abstract

**Background:**

Physical inactivity is one of the leading causes of chronic disease in Canadian adults. With less than 50% of Canadian adults reaching the recommended amount of daily physical activity, there is an urgent need for effective programs targeting this risk factor. Health*e*Steps™ is a healthy lifestyle prescription program, developed from an extensive research base to address risk factors for chronic disease such as physical inactivity, sedentary behaviour and poor eating habits. Health*e*Steps™ participants are provided with in-person lifestyle coaching and access to *e*Health technologies delivered in community-based primary care clinics and health care organizations.

**Method/Design:**

To determine the effectiveness of Health*e*steps™, we will conduct a 6-month pragmatic randomized controlled trial with integrated process and economic evaluations of Health*e*Steps™ in 5 clinic settings in Southwestern Ontario. 110 participants will be individually randomized (1:1; stratified by site) to either the intervention (Health*e*Steps™ program) or comparator (Wait-list control). There are 3 phases of the Health*e*Steps™ program, lasting 6 months each. The *active phase* consists of bi-monthly in-person coaching with access to a full suite of *e*Health technology supports. During the *maintenance phase I*, the in-person coaching will be removed, but participants will still have access to the full suite of *e*Health technology supports. In the final stage, *maintenance phase II*, access to the full suite of *e*Health technology supports is removed and participants only have access to publicly available resources and tools.

**Discussion:**

This trial aims to determine the effectiveness of the program in increasing physical activity levels and improving other health behaviours and indicators, the acceptability of the Health*e*Steps™ program, and the direct cost for each person participating in the program as well as the costs associated with delivering the program at the different community sites. These results will inform future optimization and scaling up of the program into additional community-based primary care sites.

**Trial registration:**

NCT02413385 (Clinicaltrials.gov). Date Registered: April 6, 2015.

## Background

Physical activity (PA) is one of the most modifiable risk factors for preventing chronic disease, yet less than 50% of Canadian adults are considered physically active [1, 2] and only a third of adults meet the recommendation of 10,000 steps per day [3]. The high level of physical inactivity combined with a poor diet amongst adults has led to higher rates of chronic disease, such as obesity, type 2 diabetes, cardiovascular disease, hypertension, cancer, osteoporosis, depression, and premature death [1–6]. Furthermore, the cost of physical inactivity in Canada is estimated at $6.8 billion per year, representing approximately 3.7% of all direct and indirect government spending [1, 7]. Fortunately, modest increases in levels of PA can reduce this spending by $2.6 billion over the next 25 years, making low-cost and effective healthy lifestyle interventions that target physical activity an important public health and economic priority in Canada [2, 7–9]. Living a physically active lifestyle provides numerous health benefits, including protection from chronic diseases and improved quality of life [1]. In fact, being physically active is associated with a greater than 50% reduction in risk for premature death, and even small improvements in physical fitness can significantly reduce one’s risk for chronic disease [1].

Research shows that many chronic diseases can be prevented by decreasing four main behavioural risk factors: physical inactivity, poor nutrition, smoking and alcohol consumption [5, 10]. Public health organizations have worked to develop many resources to address these risk factors; however, previous research has noted that those who are the most physically inactive are not aware of these resources [11] or may be unsure of how to use this information to make a change. While research interventions promoting PA and healthy eating in controlled settings have shown unequivocal results in reducing chronic disease risk under certain conditions, effective methods for implementing this evidence into everyday primary care practice requires further exploration [12–15]. This is particularly true for rural and remote regions in Canada where increased rurality leads to an increased risk for chronic disease and also limited access to cost-effective, evidence-based, chronic disease prevention programs and tools [16, 17].

The Health*e*Steps™ program was developed in response to the literature demonstrating the effectiveness of primary care-based chronic disease prevention programs [18], consultations with stakeholders and experts across Canada (including targeted discussions with knowledge users), and the need for such programs especially in rural and remote areas [19]. The Health*e*Steps™ program was developed from an extensive research base [18, 20–27]; draws on evidence from diverse areas including PA, nutrition, behaviour change, and knowledge translation; and has been refined by our experience implementing the program in diverse community settings including Family Health Teams, Community Health Centres, health clubs, and workplaces.

The Health*e*Steps™ program provides individuals with a specific plan of action to improve their PA levels, healthy eating habits, and reduce their sedentary behaviour. This is achieved through personalized coaching, grounded in the principles of Motivational Interviewing [28] and Co-Active coaching [29], and supported by innovative health services technologies, hands-on training, and widely available health promotion resources and tools. A distinct advantage of Health*e*Steps™ is the pragmatic nature of the program and ability to work within the existing workflow of an organization. While certain elements of the program must be conducted exactly as designed to follow the evidence-based protocols, other aspects are flexible. For example, the program may be conducted in-person in small groups or one-on-one; it can be run in a variety of primary care based settings; and it can be integrated with other existing programs.

## Methods

### Study aims

To conduct an outcome evaluation to determine effectiveness of the Health*e*Steps™ program in helping at-risk individuals increase PA levels (i.e., average number of steps per day), improve eating habits, and improve other health behaviours and health indicators.To conduct a process evaluation to determine acceptability of the intervention, to inform program improvement and optimization.To conduct an economic evaluation to determine the direct cost associated with delivering the Health*e*Steps™ program at different community sites, and the average cost per participant involved in the Health*e*Steps™ program.

### Study design

A 6-month, two-arm, pilot, pragmatic, randomized controlled trial (RCT) with integrated process and economic evaluations will be conducted within five clinic/health care organization settings in both urban and rural communities in Southwestern Ontario. Participants will be individually randomized (1:1, stratified by site [three sites in London, one site in Forest, and one site in Tillsonburg, Ontario Canada]) to either the intervention (Health*e*Steps™) or the comparator (Wait-list control). Participants in both groups will complete measurement sessions at baseline and 6 months; participants in the intervention group will complete additional measurements at 12 and 18 months. Participants in the comparator group will be given the opportunity to start the Health*e*Steps™ program after a 6-month delay. See Fig. 1 for study flow diagram.

**Fig. 1 Fig1:**
[figure not shown]
HealtheSteps Flow Diagram

Study recruitment will begin in May 2015 at the 5 clinic sites, with the intervention starting in June 2015. Western University Health Sciences Research Ethics Board approved this study and all participants will provide written informed consent. The pragmatic RCT portion of this study was registered on April 6, 2015 with ClinicalTrials.gov (identifier: NCT02413385).

### Recruitment of study sites & coach training

This trial was designed to recruit primary care sites and/or health service organizations as they provide greater opportunities to recruit participants at risk or diagnosed with a chronic disease. We will solicit interest from primary care community sites for participation in the trial by contacting primary care leads in target communities where they had not been previously exposed to the Health*e*Steps™ program. Sites will be recruited opportunistically through connections with the research team. A variety of staff from each site will be recruited for training to be coaches in the program. Meetings with sites will occur with the central research team to ensure the coaches are trained in the program protocol and understand the commitment required (space, coaching staff, and timelines). Health*e*Steps™ coaches will be trained by the central research team or via *e*Learning modules available through the Health*e*Steps™ website [30]. In order to keep the trial highly pragmatic, coaching sessions and measurement sessions will occur at the sites.

### Sample size

We set a recruitment target of 110 participants. Baker and colleagues [31] conducted a 12-week RCT of a pedometer-based walking program plus PA consultation in 80 community-dwelling Scottish adults [mean (SD) age: 49.2 ± 8.8 years; 79% women] who were not meeting current PA recommendations (20% withdrawal rate by 12 weeks). After 12 weeks, this study reported a difference between intervention and control groups in mean change of 3021 steps per day – favouring the intervention group. Using a pooled standard deviation of 3498 steps per day results a Cohen’s d effect size of 0.86. In order to be conservative, we reduced the effect size to 0.65, a moderate to large effect size. Thus, with 38 participants per group, our study would have 80% power at a 0.05 two-sided significance level to detect an effect size of 0.65 [32]. We estimate a dropout rate of 30% over the 6-month period, which will increase our target to 110 participants (55 participants per group). Since we have 5 sites who expressed interest in taking part in this study, we propose that each site will need to enroll 22 participants (i.e., 11 participants per group per site).

### Participant recruitment & enrollment

Participants will be recruited at the sites through poster advertisements, word of mouth, health care provider referrals, staff e-mails, and in-person recruitment booths. Those interested in participating will be contacted by the central research team and asked to attend an in-person screening session. At this session they will be screened for eligibility and if deemed eligible will take part in baseline measurements. Randomization will occur after baseline assessments. All individuals who contact a study site will be asked to report where they heard about the program. Participants who are ineligible and those who choose not to enroll in the study after initial contact will be tracked, along with reasons for ineligibility/not enrolling. Acceptability of randomization will be estimated from the percentage of participants who adhered to their allocation assignment (i.e., attend program sessions if allocated to the intervention group) and/or attend measurement sessions. Participation in the follow-up measurement sessions will be used to assess retention throughout the trial. Attendance at program sessions will be obtained from coach’s logs and will be used to assess adherence to the program.

#### Inclusion criteria

Individuals 18–85 years of age; one or more self-reported or measured risk factors for chronic disease including: body-mass index (BMI) greater than 25 kg/m^2^; less than 150 min of exercise per week; 3 or more hours sitting per day; consuming less than 8 fruit and vegetable servings per day; diagnosis of metabolic syndrome or type 2 diabetes; and clearance to participate in PA via the Physical Activity Readiness-Questionnaire (PAR-Q) or a health care provider.

#### Exclusion criteria

Individuals who are unable to comprehend the letter of information and consent documentation.

### Randomization and allocation

Following the baseline measurement, participants at each site will be individually allocated to either the intervention (Health*e*Steps™ program) or comparator (Wait-list control). The randomization sequence (1:1, stratified by site) will be computer-generated and conducted by a member of the research team who will not be involved in allocation. Following allocation, all participants (intervention and comparator groups) will receive Eating Well with Canada’s Food Guide [33] and the Canadian Physical Activity Guidelines for Adults [34].

### Adverse events

Participants will be given information at baseline on reporting adverse events to the central research team throughout their participation in the study. Adverse events are described as any injury or newly diagnosed health condition (i.e., high blood pressure, diabetes) that occurs while a participant is enrolled in the Health*e*Steps™ study, whether or not it is related to their participation in the Health*e*Steps™ program. At each coaching session, participants in both the intervention and comparator groups will be asked about any adverse events they may have experienced while they were enrolled in the Health*e*Steps™ study, and whether it was related to their participation in the program. The adverse events will be reviewed by the lead study physician and if necessary, refer participants for appropriate event follow-up. The outcome of adverse events will be followed until the end of the study.

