#### Active phase (months 0–6)

Participants assigned to the intervention group will start the Health*e*Steps™ program within three weeks of completing their baseline measurement session. Participants will receive a handbook that contains documents to help them track their progress throughout the program and will be given a pedometer to use to track their PA. The research team chose to utilize pedometers to measure step counts as they are inexpensive, easy to use, and easily interpreted by the participant and research team [35]. In total, participants will receive four bi-monthly in-person coaching sessions (occurring at months 0, 2, 4, and 6) with a Health*e*Steps™ coach who will be trained on how to create an action plan with the participant to help them work towards achieving their lifestyle prescriptions. Strategies for setting lifestyle prescriptions are based on S.M.A.R.T. goal setting principles (specific, measurable, attainable, realistic, and timely for the participant), as goal setting has been found to produce positive behaviour change in adults [36]. The lifestyle prescriptions and supports are as follows:
*Exercise Prescription:* The exercise prescription focuses on making incremental changes in the amount of time the participant engages in moderate to vigorous activity or the amount of time they exercise within their target heart rate zone, up to the recommended 150 min/week. At each program session, participants will complete a sub-maximal fitness test, the Step Test and Exercise Prescription tool (STEP™ Test) [37]. Based on their fitness score from this test (i.e., predicted maximal oxygen uptake, VO2max), participants will receive an exercise prescription with a personalized target heart rate (65–85% of estimated maximum heart rate) for exercise. Coaches will then encourage participants to exercise at their training heart rate and/or at a rating of 5–8 on the 10-point modified Borg Rating of Perceived Exertion scale during aerobic activities [38]. The Health*e*Steps™ coach will collaborate with the participant to set a weekly target of exercise minutes that includes frequency, duration, and type of exercise to facilitate achievement of their exercise prescription.

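### The adverse-event definition leaves out worsening of existing disease and symptomatic events without an injury or new diagnosis, although people with chronic disease are recruited

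*Protocol article*

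**What the plan says.** All statements are from the protocol article.

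- **Adverse events** gives the definition: "Adverse events are described as any injury or newly diagnosed health condition (i.e., high blood pressure, diabetes) that occurs while a participant is enrolled". Causality is left open, since an event counts "whether or not it is related to their participation" in the program. Participants are told at baseline how to report adverse events to the central team. At coaching sessions, participants in both groups "will be asked about any adverse events they may have experienced while they were enrolled". The lead study physician reviews the adverse events and refers participants where needed, and outcomes are followed to the end of the study.
- **Recruitment of study sites & coach training** explains the choice of primary care sites and health service organizations: "they provide greater opportunities to recruit participants at risk or diagnosed with a chronic disease".
- **Inclusion criteria** admits ages 18 to 85 with at least one risk factor. One of the alternatives is "diagnosis of metabolic syndrome or type 2 diabetes". Clearance for physical activity by PAR-Q or a health care provider is also required.
- **Exclusion criteria** has one entry: "Individuals who are unable to comprehend the letter of information and consent documentation".
- **Active phase (months 0–6)** describes four coaching sessions for the intervention group. "At each program session, participants will complete a sub-maximal fitness test", and an exercise prescription with a personal target heart rate follows from the result.

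**The concern.** The definition suits a population that enters healthy, in whom harm would appear as an injury or a first diagnosis. This trial also enrols people who already have a diagnosis. For them, the most likely form of disease-related harm is that the existing condition gets worse, and that is neither of the two things the definition admits. The same holds, for any participant, for chest pain or a faint during a step test that passes without an injury or a diagnosis.

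The term carries through the whole reporting chain. Participants are told how to report adverse events and are asked about adverse events, and the physician reviews adverse events. No broader question about change in health is described. An event outside the definition therefore has no stated way into the safety record or to physician review. If staff report such events anyway, they depart from the written rule, and practice may differ across the five sites.

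**Working it through.** No arithmetic applies, because the point depends on the wording of a definition and not on a rate or a sample size. The check is to apply the definition to plausible events and see which qualify.

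**Does any other text widen the definition?** The clause on relatedness widens causality, not the type of event. The sections on eligibility, the intervention, data collection and analysis add nothing on worsening, exacerbation, hospitalisation or death.

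**Events that do not qualify:**
- Known type 2 diabetes, with a hypoglycaemic episode that causes no injury: no injury and no new diagnosis.
- Known hypertension that becomes harder to control: no injury and no new diagnosis.
- A known condition leading to hospitalisation or death, with no new diagnosis: neither category is met.
- Chest pain or a faint during the step test, with no injury and no diagnosis: neither category is met.

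**Events that do qualify:**
- A faint during the step test that causes an injury.
- A new cardiac diagnosis in a participant with known diabetes.
- A first diagnosis of high blood pressure in a participant with known diabetes, or the reverse.

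**Could the excluded events surface elsewhere?** Tables 1 and 2 list weight, BMI, waist circumference, blood pressure and the EQ-5D visual analog scale. These are measured at baseline and 6 months in both groups, and at 12 and 18 months in the intervention group only. A sustained rise in blood pressure or a fall in self-rated health would appear there. Three limits apply:
1. These are outcome measures with no stated link to safety review.
2. They are taken six months apart, so they would not document an acute episode.
3. No glucose or HbA1c measure is listed, so worsening glycaemic control in type 2 diabetes, a disease named in the inclusion criteria, has no direct measure in either the adverse-event data or the outcome data.

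**Who is affected?** An existing diagnosis is only one of several alternative ways to qualify; others are sitting 3 or more hours a day or eating fewer than 8 fruit and vegetable servings. The article gives neither the expected share with existing disease nor a rate of worsening, so the number of uncounted events cannot be calculated. The definition applies to both arms, but only the intervention arm has the fitness tests and exercise prescription during the first six months.

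**The case against.** The strongest case on the other side has five parts.

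- **Scheduled outcomes record some worsening.** This is correct. A reader might infer that deterioration in existing disease is never recorded at all, and the documents do not support that. What stands is that it is not recorded as an adverse event.
- **New diagnoses and injuries still count, whatever the history.** Also correct. A reader might infer that the definition captures nothing in participants with existing disease. It does capture complications with their own diagnosis, and injuries. The gap is what remains after those.
- **Participants are cleared for activity before entry.** Clearance lowers the risk at entry but does not record what happens afterwards.
- **Safety is not a stated aim.** The Abstract and Study aims rest on effectiveness, acceptability and cost. A reader might infer that a falsely clean safety record would be used to support scale-up. Nothing in the article says that an adverse-event tally will be used in this way, so that reading is not supported. The trial nevertheless sets up adverse-event collection with physician review, and that process should work for the people enrolled.
- **The article is condensed.** Fuller reporting instructions or forms may exist. This lowers confidence somewhat. However, the article does not leave the definition to another document: it states one, and as stated it has two categories.

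**Conclusion.** The point holds in a limited form. As written, worsening of a condition present at baseline does not meet the adverse-event definition. Nor does a symptomatic event during fitness testing or exercise that leads to neither an injury nor a new diagnosis. Neither has a stated route to review by the lead study physician. This sits badly with a recruitment strategy that reaches people with chronic disease and an intervention built on fitness tests and exercise prescriptions.

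The size cannot be stated. A reader might multiply an assumed prevalence of chronic disease by the 55 participants per group, but that would count people who have a diagnosis, not people who deteriorate, and the article gives neither rate.

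The primary comparison of steps per day is unaffected. What is weakened is any statement about harms. The conclusion assumes that sites apply the definition as printed and that no unseen form widens it.

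**What to change.** In the Adverse events section and on the adverse-event form, add two items, each counted whether or not it is thought related to the program:
1. worsening of a condition present at baseline, including hospitalisation or death from it;
2. symptomatic events during fitness testing or exercise.

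Elicitation must change with the definition. Events are now asked about at coaching sessions, but the Comparator group section gives that arm no intervention for the first six months. A wider definition asked about only at coaching sessions would raise capture in the intervention arm alone. Put the same question at the same time points to both arms, for example at the 6-month measurement session that both attend.

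To judge worsening, the conditions present at entry must be on record. Table 1 lists health-related information at baseline but does not show whether it covers disease status, so confirm that it does.

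The cost is a short addition to the text, a form edit and one common question at a visit already scheduled. There will be somewhat more events to record and review, and the event count will look less favourable.

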### Comparator group (wait-list control)

This group will continue with usual activities without intervention from the study team for the first 6-month period. After the 6 month measurement sessions are completed, participants allocated to this group will be given the opportunity to start the 6-month Health*e*Steps™ program.

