### Data collection

#### Outcome evaluation

The outcome measures will be taken at baseline and 6 months in both groups, and then again at 12 and 18 months in the intervention group only (see Table 1). Home visits will be conducted when participants are unable to attend follow-up measurement sessions at the sites to increase participant retention throughout the long-term follow-up. Data sources will include self-reported PA, participant demographics, clinical measures, and the completion of health related information and questionnaires (See Table 2).

**Table 1 Tab1:** Screening and measurement sessions schedule

Measurement	Screening	Baseline	6-month	12-month (Intervention Group only)	18-month (Intervention Group only)
*Screening & Eligibility Measures*					
Participant Self-Reports at Screening	X				
Pre-Randomization ID #	X				
Letter of Information & Consent Form	X			X	
PAR-Q	X				
Health Care Provider Clearance Form	X				
Eligibility Form	X				
Group Allocation		X^a^			
Participant ID#		X^a^			
*Baseline Health Information*					
Demographics & Health Related Information		X			
*Clinical Measures*					
Age	X	X^b^			
Height	X	X^b^	X^b^	X^b^	X^b^
Weight	X	X^b^	X	X	X
Body Mass Index	X	X^b^	X	X	X
Waist Circumference		X	X	X	X
Blood Pressure		X	X	X	X
*Self-Reported Physical Activity*					
Average Steps/day (Step Count Outcome Tracking Form)		X	X	X	X
International Physical Activity Questionnaire		X	X	X	X
*Self-Reported Eating*					
Modified DINE		X	X	X	X
Starting the Conversation		X	X	X	X
*Health-Related Quality of Life*					
EQ-5D-3 L		X	X	X	X

^a^Occurs at Randomization & Allocation Session

^b^Use number recorded at Screening Session

**Table 2 Tab2:** Data collection & measurement protocol

Outcome Measure	Equipment required	Protocol
*Self-Reported Physical Activity*		
Average steps/day	Pedometer (Yamax Digiwalker SW-200 with security strap)	• Participants wear pedometers during waking hours for a 7-day period (putting pedometer on upon waking and removing immediately before sleeping), but not during showering/bathing • Participants are asked to wear the pedometer at the waist, centered over their most dominant foot • Participants record the number of steps completed each day on a paper-based tracking form

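### During the randomised six months the scheduled adverse-event question reaches only the intervention arm, so any by-arm account of harms would probably over-count events in that arm

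*Protocol article*

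**What the plan says.** The Adverse events section sets up two routes for collecting events.

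- **Self-report, open to everyone:** "Participants will be given information at baseline on reporting adverse events to the central research team throughout their participation in the study".
- **Active questioning:** "At each coaching session, participants in both the intervention and comparator groups will be asked about any adverse events they may have experienced". The question covers the time in the study.

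The definition is broad. An injury or new diagnosis counts "whether or not it is related to their participation in the" program, so background events are expected in both arms.

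The timing of coaching is given elsewhere. Under Active phase, the intervention arm has "four bi-monthly in-person coaching sessions (occurring at months 0, 2, 4, and 6"), the first within three weeks of baseline. Under Comparator group: "This group will continue with usual activities without intervention from the study team for the first 6-month period". The same section continues: "After the 6 month measurement sessions are completed, participants allocated to this group will be given the opportunity to start" the program.

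The contacts that both arms share are the measurement sessions. Under Outcome evaluation: "The outcome measures will be taken at baseline and 6 months in both groups". The statistical analysis section describes contrasts for the primary and secondary outcomes and does not mention adverse events.

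**The concern.** The active question is promised to both groups but hangs on a contact that one group does not have while the groups are being compared. In months 0–6 intervention participants are asked repeatedly, and comparators are left to report on their own initiative. Comparators who later start the program are asked afterwards, looking back over six months or more. For those who decline it, the article describes no scheduled question at all.

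Recorded events depend on both the true risk and how hard one looks. With a definition that takes in unrelated events, only equal ascertainment separates background events from program effects. The program prescribes exercise and a fitness test at each session for adults up to age 85, so readers will want to know about injuries. A by-arm count from months 0–6 would be the natural place to look, and it would probably lean against the program. An analysis plan written later cannot repair this, because the imbalance arises when the data are collected.

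**Working it through.** **Step 1. Scheduled questions in months 0–6, from the text.**

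| | Intervention | Wait-list |
|---|---|---|
| Coaching sessions (Active phase; Comparator group) | 4 (months 0, 2, 4, 6) | 0 |
| Scheduled adverse-event questions | 4 | 0 |
| Informative about follow-up | about 3 | 0 |
| Self-report to the central team | yes | yes |

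The month-0 session falls within three weeks of baseline, so there is almost no follow-up for it to capture. That leaves months 2, 4 and 6.

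**Step 2. What unequal questioning could do.** The document gives no event rate and no capture rate, so every input here is an assumption except the 55 per group (Sample size section). Take the same true risk, 20%, in both arms.

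Recorded participants with an event = 55 × 0.20 × capture = 11 × capture.

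- Asked, capture 80–90%: 11 × 0.8 = 8.8 to 11 × 0.9 = 9.9.
- Self-report only, capture 30–50%: 11 × 0.3 = 3.3 to 11 × 0.5 = 5.5.

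The apparent risk ratio is the ratio of the capture rates. The true risk and the group size cancel.

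- Lowest: 0.8 / 0.5 = 1.6 (8.8 against 5.5).
- Highest: 0.9 / 0.3 = 3.0 (9.9 against 3.3).

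If self-report were better than that, say 70% against 90%, the ratio would be 0.9 / 0.7 = 1.29. It reaches 1.0 only if self-report captures as much as asking.

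**Step 3. Allowing for delayed coaching.** Suppose self-report captures 50%, a proportion u of comparators take up the program, and a proportion r of the events missed so far are recalled at their first session. Then:

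comparator capture = 0.5 + 0.5 × u × r; ratio = 0.9 / comparator capture.

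| Uptake u | Recall r | Comparator capture | Apparent ratio |
|---|---|---|---|
| 0.5 | 0.5 | 0.625 | 1.44 |
| 0.5 | 0.8 | 0.700 | 1.29 |
| 0.7 | 0.5 | 0.675 | 1.33 |
| 0.7 | 0.8 | 0.780 | 1.15 |
| 0.9 | 0.5 | 0.725 | 1.24 |
| 0.9 | 0.8 | 0.860 | 1.05 |

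The corresponding ratio without recovery is 0.9 / 0.5 = 1.8. Recovery brings it to 1.05–1.44. This assumes that events recalled after month 6 are dated and counted back into the randomised period.

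**Step 4. The plan's own figure.** The only design calculation in the article is the sample size. A standardised effect of 0.65, two-sided 0.05 and 80% power gives 38 per group, which reproduces. Allowing for 30% dropout, 38 / 0.7 = 54.3, rounded up to 55 per group or 110 in all. Adverse events play no part in it.

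**The case against.** The strongest reply is that no planned analysis is harmed. The aims are effectiveness, acceptability and cost. Adverse events are not among the outcome measures, and the purpose stated for collecting them is physician review and follow-up of the individual. This stands. A reader might infer that the trial's randomised safety comparison is biased, but the article plans no such comparison. The point applies to any by-arm tabulation or statement on harms, not to a named test.

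Second, the sentence about both groups can be read as true: comparators who take up the program will have coaching sessions, and the question looks back over their time in the study. That also stands in part. Nothing says that comparators are questioned during months 0–6. But the later question depends on an optional program and on long recall, so the imbalance shrinks without disappearing.

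Third, a reader might infer that comparator events go uncollected. They do not, because self-report is open to both arms from baseline. Comparator events are likely to be under-ascertained, not lost altogether.

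Fourth, Table 1 shows no adverse-event item at the 6-month session, but it is a schedule of screening and outcome measures in a condensed article. Its silence does not prove that no such form is used, and I do not rely on it. The finding rests on what the Adverse events section states, set against the coaching schedule.

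Last, four questions against none overstates the contrast, since the month-0 question has little to capture.

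**Conclusion.** The point holds in a limited form. Followed as written, the plan gives scheduled questioning in the intervention arm and self-report alone in the comparator arm throughout the randomised period: about three informative questions against none. That much follows from the text.

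The likely consequence is an over-count in the intervention arm in any by-arm account of harms. The direction rests on one assumption, that people asked about events report more of them than people left to volunteer them. The document does not support saying that the program will look more harmful, or by how much. The ratios of 1.6–3.0 without recovery and about 1.05–1.44 with it are illustrations on assumed inputs.

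The defect is worth correcting because it is cheap to correct. It does not touch the primary outcome, the sample size or the efficacy analysis.

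**What to change.** 1. At the 6-month measurement session, put one identical adverse-event question to every participant in both arms, covering the time since randomisation and asked before any comparator coaching starts.
2. Base any between-arm summary of harms on that common question. List events reported at coaching sessions separately, as intervention-arm data.
3. Reword the Adverse events section to say that the coaching-session question reaches comparators only after month 6, and only if they start the program, so that it agrees with the Comparator group section.

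The cost is one item on a form at a session both arms already attend, and a sentence or two of text. The downside is reliance on six-month recall. That recall will not be perfectly equal, because earlier coaching questions may help intervention participants remember, so the report should acknowledge some residual asymmetry. The better-dated coaching-session reports are kept but stay out of the between-arm contrast.
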